#### Qualitative interviews

As this study will assess a new model of diabetes care in NZ, a series of qualitative studies will be completed to explore the lived experiences of participants with a particular focus on Hub satisfaction and acceptability, as well as general experiences using AID. Semi-structured interviews of 50–60 min will be conducted with a wide sample of participants enrolled in the Hub. Participants will be invited to include whānau (family) in these interviews according to their own preferences. Interviews will be conducted via video or phone call, or in-person if requested, after AID has been started and participants have been transitioned back to their usual care teams. We will conduct three qualitative sub-studies, with participants and their whānau (families), (Māori participants, Pacific participants and non-Māori, non-Pacific participants, each with a sample size of 10–15 participants). Potential participants from the main study will have the option to consent to the qualitative sub-study when completing the online consent form.

A further objective of this study is to determine whether the experience diabetes care providers obtain by being employed by the Hub (i.e., clinical staff) is effective in improving their self-efficacy in preparing, training and managing patients using AID. All clinical staff employed by the Hub will be invited to consent to participate in a qualitative interview and to complete a self-efficacy questionnaire via an online participant information and consent form. If consented, they will complete the self-efficacy questionnaire at baseline and again upon leaving the Hub, and to participate in a semi-structured interview. Demographic information will also be collected (e.g., age, sex, occupation).

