### Objectives

This study has four main objectives: (1) To determine the effectiveness and safety of a remote Hub to start AID and address inequities in care; (2) To investigate using qualitative methodologies whether the Hub is acceptable for both people and whānau (families) living with T1D and their health care teams, and how the model can be improved; (3) To determine whether inviting diabetes care providers to partake in the Hub is effective in improving knowledge about, and training methods for AID; (4) To determine the cost effectiveness of the Hub in starting AID compared to current models across districts in NZ.

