#### 12-weeks (primary end-point)

At 12 weeks, participants will be asked to complete the DTSQ change and EQ-5D questionnaires, and to attend their nearest laboratory for a final measurement of HbA1c. CGM data will be downloaded from participants’ online profile. Access to participant profiles will be retained on the study accounts to allow for remote review at 6-months for the purpose of data retrieval. Participants will be referred back to their usual care team at 12-weeks post AID start or earlier if stable (e.g., If TIR is > 70% or individualised TIR target is met with no significant hypoglycaemia or other concerns, the patient will be discharged before 12 weeks). This will involve a transfer of all CGM and HbA1c data back to their usual care teams to ensure optimal ongoing support. If for any reasons the Hub team do not believe discharge at 12 weeks is safe, then this will occur at a later date when appropriate.

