#### Qualitative interviews

In brief, audio recordings from the semi-structured interviews with both participants and clinical staff will be transcribed verbatim, and recordings will be deleted thereafter. Nvivo software will be used to conduct a thematic analysis to identify Hub satisfaction and acceptability (for interviews with study participants), and factors that supported and hindered clinician self-efficacy in managing AID (for interviews with clinical staff). Themes will be compared between members of the analysis team until consensus is reached. For study participants, age, sex, insulin regimen, and duration since diagnosis will be taken from clinical records in order to describe the sample. For clinical staff, age, sex, and occupation/role will be collected in order to describe the sample. The qualitative sub-study of the experience of Māori participants in the ACCESS-AID study will be guided by the principles of decolonising methodologies [41] challenging western research practices to centre the needs, voices, and expectations of Māori participants and whānau. Interviews with Pacific participants will be managed in culturally appropriate ways with consideration to relevant Pacific health models.

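### Interviews follow AID start and transfer back to usual care, so enrolled people who never started or left before transfer have no stated route into the acceptability findings

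*Protocol article*

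**What the plan says.** All references are to the protocol article.

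- **Objectives, item 2.** The qualitative work is to establish whether the Hub is acceptable to people with diabetes, their families and their care teams, "and how the model can be improved".
- **Procedures, Qualitative interviews (who).** Semi-structured interviews "will be conducted with a wide sample of participants enrolled in the Hub". There are three sub-studies (Māori, Pacific, and non-Māori non-Pacific participants), "each with a sample size of 10–15 participants".
- **Procedures, Qualitative interviews (when).** Interviews take place "after AID has been started and participants have been transitioned back to their usual care teams".
- **Procedures, Qualitative interviews (consent).** Potential participants from the main study "will have the option to consent to the qualitative sub-study when completing the online consent form". That form comes before the baseline assessments and before AID start.
- **Outcomes, Qualitative interviews.** The participant interviews undergo "thematic analysis to identify Hub satisfaction and acceptability (for interviews with study participants"). They are thus the source of the acceptability finding.
- **12-weeks (primary end-point).** "Participants will be referred back to their usual care team at 12-weeks post AID start or earlier if stable". Transfer may also come later than 12 weeks if the Hub team thinks discharge at that time unsafe.

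**The concern.** The stated frame is everyone enrolled, but the interview is triggered by two later events. For a person to whom one of those events never happens, a rule about timing works as an exclusion.

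The people affected enrolled and then did not start AID, or left before being handed back. Several steps lie between consent and the first day on AID: questionnaires, an HbA1c request, a telehealth consultation, device choice and prescriptions, at least two weeks of CGM data, a carbohydrate assessment and the training session. Someone lost at one of these steps can say directly what the Hub might change.

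The article presents barriers to access as the reason for the study, and its prioritisation score favours people expected to meet them. Losing these accounts therefore weakens the part of Objective 2 about improving the model, and may do so most in the priority groups for whom separate sub-studies are planned.

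**Working it through.** The point rests mainly on reading the text. The article states no figure for non-start or early leaving, so there is none to reproduce. The main-study power statement has no bearing here.

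**Step 1. Apply the two interview conditions to each kind of enrolled person.**

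| Enrolled person | AID started? | Transferred back? | Stated route to interview? |
|---|---|---|---|
| Started and handed back, whatever the result | Yes | Yes | Yes |
| Started, stopped AID, then handed back | Yes | Yes | Yes, on a literal reading |
| Stopped AID after handover | Yes | Yes | Yes |
| Started, left the Hub before handover | Yes | No | None stated |
| Never started AID | No | Not applicable | None |
| Withdrew all consent | Any | Any | None under any design |

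The fourth and fifth rows are the gap. The fifth follows from the text without any assumption. The fourth depends on whether leaving early counts as being transferred back, which the article does not define.

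**Step 2. Look for another source.**

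- The satisfaction and health-status questionnaires at 12 weeks measure treatment satisfaction and health state, not why someone did not start or left.
- The Statistical analysis section will tabulate numbers referred, enrolled and started. That counts non-starters but gives no reasons.
- The same section's possible exploration of barriers to uptake compares regions, not people.

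**Step 3. Illustrate the size.** Total interviews: 3 × 10 = 30 to 3 × 15 = 45. Let r be the share of enrolees who never start or leave before transfer. r is an assumption, shown over a range.

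- Expected number in a proportionate sample = n × r.
- Chance that one sub-study of size n drawn at random holds at least one = 1 − (1 − r)^n.

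| Assumed r | Expected among 30 to 45 | Chance of at least one, n = 10 | Chance of at least one, n = 15 |
|---|---|---|---|
| 2% | 0.6 to 0.9 | 18.3% | 26.1% |
| 5% | 1.5 to 2.25 | 40.1% | 53.7% |
| 10% | 3.0 to 4.5 | 65.1% | 79.4% |
| 20% | 6.0 to 9.0 | 89.3% | 96.5% |

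Under the current wording the number of never-starters is 0 at every r. The last two columns also show that dropping the conditions would not be enough if r is low, because a random sub-study of 10 to 15 could easily contain no such person. That is the reason for including some on purpose.

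**The case against.** The case against has real force on several points.

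- **The clause is about mode and timing.** The frame is given separately as enrolled participants, and no sentence names withdrawal, stopping or a poor result as an exclusion. This is true, but an interview timed to an event that never occurs cannot take place. The two sentences need to be reconciled.
- **An article condenses the full protocol.** Detailed recruitment may well be left to that document, and its absence here would be no finding. The point, however, concerns a condition that the article states.
- **The timing has a purpose.** The interviews also cover general experience of using AID, which requires a start. This justifies the condition for that topic but not for Hub acceptability.
- **Small thematic studies estimate no acceptability rate.** This is correct, so a proportionate sample is only a yardstick for scale and the bias cannot be put as a number.

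A reader might also infer more than the text supports. It does not admit only people for whom the Hub worked, since transfer is not tied to success. It does not exclude people who stopped AID: those handed back, or who stopped after handover, meet both conditions. It does not follow that the interviews will contain no one who failed to complete, or that acceptability will certainly be overstated. People who withdrew all consent are beyond reach whatever the wording.

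**Conclusion.** The concern holds in a narrow form. Enrolled people who never started AID have no route into the interviews, and those who left before transfer have none stated. This conflicts with the promise to sample widely among those enrolled, and it leaves Objective 2 without the accounts of people who may have found the Hub hardest to use. A tilt towards those who stayed to handover is likely. Its size is unknown, because it depends on how many enrolees do not start or leave early and on how their views differ, and the article gives neither. The range of about 1 to 9 interviews in 30 to 45 rests wholly on the assumed 2% to 20%. This is a modest improvement to a secondary, qualitative component and changes no figure in the protocol.

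**What to change.** Keep the three sub-studies and their sample sizes, and amend the sampling wording in Procedures, Qualitative interviews:

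1. Make every enrolee who consented to the sub-study eligible for interview, whatever their AID start or transfer status.
2. In each sub-study, purposively include a few people who did not start or who left before transfer and have not withdrawn consent. Interview them when they leave.
3. Leave the present timing in place for everyone else.

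Consent to interview is already offered on the enrolment form and interviews are by video or phone, so no new consent step or visit is needed. The cost is slightly fewer completer interviews within each 10 to 15, and some extra effort because these people may be harder to reach.

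If the sponsor prefers to keep the present rule, the report should limit its acceptability conclusion to people who started AID and were transferred back.

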#### 6-months

At 6-months, CGM data uploaded to study online accounts will be reviewed to determine if any improvements in glycaemia are maintained followed transfer back to usual care teams. After this review has been completed, participant profiles will be removed from study accounts.

### Outcomes

The primary outcome of this study is to assess the implementation effectiveness of the Hub. Secondary outcomes of this study include intervention effectiveness, safety and acceptability, psychosocial measures, nutrition education effectiveness, cost-effectiveness and clinical staff self-efficacy and intervention acceptability.

#### Implementation effectiveness

Implementation effectiveness of the Hub, at facilitating AID starts and addressing inequities in care, will be assessed by determining the number and characteristics of people who are referred and enrolled by the Hub, and the time to discharge on AID. Counts of AID starts will be compared by provider (Hub versus all others) and over time (weekly from 12 months prior to Hub implementation until study end). Incidence proportions of new AID starts, and prevalence for overall AID usage, will be estimated nationally and by region for priority populations; Māori, Pacific, those living in rural areas, and those living in areas of highest socioeconomic deprivation as measured by the NZ deprivation index [37].

#### Intervention effectiveness

Intervention effectiveness of AID will be determined by estimating participants’ changes in standard glycaemic metrics between baseline and 12-weeks including: HbA1c, time in range ([TIR], 3.9 to 10.0 mmol/L [70 to 180 mg/dL]), time in tight range ([TING/TITR] 3.9 to 7.8 mmol/L [70 to 140 mg/dL]), time below range ([TBR] < 3.9mmol/L [< 70 mg/dL]), and time < 3mmol/L (< 54 mg/dL), > 10mmol/L (> 180 mg/dL) and > 13.9mmol/L (> 250 mg/dL). CGM metrics will also be assessed between baseline and 12-weeks, and again at 24-weeks (6 months) to determine whether any benefits are maintained following discharge, These include glycaemic management index (GMI), glycaemic outcomes differentiated as 24 h, day (0600–2359 h) and night (0000–0559 h), co-efficient of variation (CV_glucose_), and mean sensor glucose +/-SD.

#### Intervention safety

Intervention safety will be assessed by the occurrence of serious adverse events (SAEs) including death and hospital admissions for diabetic ketoacidosis (DKA), severe hypoglycaemia (defined as coma or convulsion requiring assistance from others) and hyperglycaemia. Participants will be instructed to notify study staff immediately in the event of any SAE related to the study, as outlined above. Incidence will be calculated for study participants and compared to controls utilising national data captured by Health New Zealand.

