#### Safety

SAEs will be managed as outlined in Sect. 2.6.3. All SAEs will be reported to the principal investigators of the study within one day of occurrence. Participants will also be advised to notify study staff of any adverse events related to the devices. This information will be used for internal safety monitoring. Technical support will be available to participants 24 h a day, and will be provided by device specific technical support services, as per usual care. Any device deficiencies (e.g., inaccurate labelling, device malfunction), will be recorded and reported to the device manufacturers as per usual practice.

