### Statistical analysis

Pharmac, NZs pharmaceutical funding agency, estimates there are 18,000 to 21,000 people with pancreatic insufficiency (mostly T1D) living in NZ who would be eligible for funded CGM [11], of whom 85–90% were not using AID in 2023. We believe the Hub will facilitate approximately 500 new AID starts per year (provided by 2.4 full time equivalent clinical staff, per year).

A sample size of 500 or more participants will provide > 90% power, with a two-sided alpha of 0.05, to detect small changes in continuous outcomes (effect sizes ≥ 0.15) and estimate binary outcomes to within +/- 5%.

Numbers of people referred to the Hub, enrolled, and started on AID will be tabulated by the key demographic and clinical variables required for calculation of the prioritisation score as listed under Sect. 2.5.1.

Incidence proportions, stratified by region and priority subpopulations, will be calculated as the number of AID starts divided by the number of eligible people not on AID as estimated from national administrative datasets. For comparisons with other providers, an individual will be considered to have started on AID on the date they are first dispensed a subsidised pump as recorded by Health New Zealand.

Interrupted time series analysis will be used to investigate the impact that the Hub has on the rate of new AID starts nationally, and by region, Absolute numbers and incidence proportions of new AID starts will be calculated for consecutive time periods and displayed graphically. Generalised linear (Poisson) regression models will be used to estimate changes in the in the numbers and incidence of new AID starts before versus after deployment of the Hub. Differences between regions, such as workforce capacity, may be explored in models to identify facilitators and barriers to AID uptake.

Intervention effectiveness will be confirmed by descriptively summarising changes in Hub participants’ HbA1c and CGM metrics before versus after starting on AID.

National laboratory and CGM data is not available for those not enrolled in the study.

Incidence rates of adverse events will be calculated for study participants after AID start and compared to control populations utilising generalised linear regression models, adjusting for demographic factors (age, gender, ethnicity, NZ deprivation index). Controls will included study participants prior to AID start and non-study people with type one diabetes who have and have not started on AID.

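### The SAE instruction to participants is narrower than the safety outcome and the all-SAE rule, and the source of participants' event counts for the control comparison is unclear

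*Protocol article*

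**What the plan says.** Three parts of the Protocol article bear on how serious adverse events (SAEs) are collected and compared.

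- **Outcome definition** (*Intervention safety*). The outcome is the occurrence of "serious adverse events (SAEs) including death and hospital admissions for diabetic ketoacidosis (DKA), severe hypoglycaemia" and hyperglycaemia. No causal condition is attached.
- **Instruction to participants** (same section, next sentence). "Participants will be instructed to notify study staff immediately in the event of any SAE related to the study, as outlined above".
- **Reporting upwards** (*Safety*). "All SAEs will be reported to the principal investigators of the study within one day of occurrence". This has no relatedness limit. In the same section a relatedness limit is applied only to participants' reports of device adverse events.

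On the comparison, *Intervention safety* says: "Incidence will be calculated for study participants and compared to controls utilising national data captured by Health New Zealand". *Statistical analysis* adds: "Incidence rates of adverse events will be calculated for study participants after AID start and compared to control populations utilising generalised linear regression models". It then defines the comparators: "Controls will included study participants prior to AID start and non-study people with type one diabetes", both those who have and those who have not started AID.

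**The concern.** The instruction to participants carries a qualifier that neither the outcome definition nor the all-SAE rule contains. A participant admitted with DKA during an unrelated illness could reasonably conclude that the admission had nothing to do with the study and say nothing. The rule that every SAE reaches the principal investigators then fails at its first step.

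Two things are at stake. The first is internal safety monitoring, which can act only on events that staff hear about. The second is the safety comparison, which belongs to the first study objective. If participants' events were counted from filtered self-reports and controls' events from national records, events would be lost on one side only, and the loss would make the Hub look safer.

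**Working it through.** **Step 1. The reporting chain.**

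| Step | Section | Events covered |
|---|---|---|
| Outcome | *Intervention safety* | SAEs, including death and the named admissions; no relatedness condition |
| Participant to staff | *Intervention safety* | SAEs related to the study, with a pointer back to the list |
| Staff to principal investigators | *Safety* | All SAEs, within one day of occurrence |

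The middle step feeds the last one and is worded more narrowly than either neighbour.

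**Step 2. Other routes by which staff could learn of an event.** *Follow up* schedules 2 reviews on days 1 and 2, 3 in weeks two to four, and 2 in months two and three: 2 + 3 + 2 = 7, with more or fewer if clinically required. The topics it names do not include asking about admissions, although the list is open-ended. The *12-weeks* section allows discharge before 12 weeks, and the *6-months* section describes a CGM review only. Between contacts and after discharge, the only route the article describes is that the participant tells the Hub.

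**Step 3. The one-day clock.** It starts at occurrence. A remote team cannot report an admission or a death before it knows of it, so the rule can be broken without anyone being at fault, whatever is decided about relatedness.

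**Step 4. The plan's own figures.** *Statistical analysis* states: "A sample size of 500 or more participants will provide > 90% power, with a two-sided alpha of 0.05", for effect sizes of at least 0.15, and precision within 5 percentage points for binary outcomes. One-sample (paired) normal approximation:

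- Power = Φ(0.15 × √500 − 1.960) = Φ(3.354 − 1.960) = Φ(1.394) = 0.918.
- Half-width at p = 0.5: 1.96 × √(0.25/500) = 0.044.

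Both reproduce. Neither measures SAE capture; the article gives no SAE rate and no capture fraction.

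**Step 5. Size of the bias, if the sources differ.** Let c be the fraction of participants' SAEs that is captured. Assume complete capture in controls and the same event definition in both groups. Then

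observed rate ratio = c × true rate ratio.

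| c (assumed) | True 1.00 seen as | True 1.25 seen as |
|---|---|---|
| 1.0 | 1.00 | 1.25 |
| 0.9 | 0.90 | 1.13 |
| 0.8 | 0.80 | 1.00 |
| 0.5 | 0.50 | 0.63 |

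At c = 0.8 a true 25% excess disappears. At c = 1, which is the case when one complete source serves both groups, nothing is distorted.

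**Step 6. How few missed events this takes.** 500 participants followed for 12 weeks give 500 × 12/52 = 115.4 person-years. At assumed SAE rates of 0.02, 0.05 and 0.10 per person-year, the expected counts are 2.31, 5.77 and 11.54. One missed event then means c = 1 − 1/2.31 = 0.57, 1 − 1/5.77 = 0.83 or 1 − 1/11.54 = 0.91. The rates are illustrative; the point is that counts over 12 weeks may be small.

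**The case against.** The strongest reply is that the comparison may never use self-reports. The sentence on incidence can be read as national data for both groups. The comparators include participants before they start AID; those events precede study reporting and most naturally come from national records linked to the participants, which would then also be available after AID start. The study is run in partnership with Health New Zealand, and the only stated limit on national data concerns laboratory and CGM results for people outside the study. This stands. A reader might infer that the plan under-counts Hub events against all-cause national controls. The documents do not support that: nowhere do they say that participants' counts come from self-report, and nowhere do they call control events all-cause. The named admissions are diabetes-specific, and only death has no stated cause.

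A second reply is that the closing words of the instruction point back to the list, so that a study-related SAE may simply mean a listed SAE. On that reading a DKA admission would be notified. This softens the conflict, and it rules out saying that participants are told to report only events they judge to be caused by the study. It does not remove the qualifier, which a lay reader can still take as a test of cause.

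A third reply is that participant-to-staff and staff-to-investigator reporting are different steps, and that staff also review device data and are in touch with usual care teams. That is true, but the article does not describe either as a way of finding SAEs, and the second step can be no more complete than what reaches it.

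Finally, detailed SAE procedures commonly sit in the full protocol. Their absence here is not the point; the point is what the printed sentences say.

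**Conclusion.** The point holds in two parts of different strength.

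1. **The wording is inconsistent.** The participant instruction is narrower than the outcome it serves and than the all-SAE rule. Read literally, it allows filtering by perceived cause and weakens internal safety monitoring. This does not depend on where the analysis data come from. The number of events that would be lost cannot be derived from the article.

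2. **The source of participants' event counts after AID start is ambiguous.** If self-reports are compared with national records, the rate ratio is multiplied by c and favours the Hub: 0.90 to 0.50 for a true 1.00 over the assumed range of c from 0.9 to 0.5. If national records serve both groups, this bias is absent, and the pre-AID comparator makes that reading plausible. The bias is therefore conditional, and the values of c are assumptions.

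It is worth correcting because the remedy is almost free and the possible error runs in the reassuring direction on a safety outcome.

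**What to change.** - In *Intervention safety* and in the participant instructions, delete the words limiting reports to study-related SAEs, so that participants report every listed SAE whatever they think caused it.
- Reconcile that sentence with the all-SAE rule in *Safety*, and start the one-day clock when the Hub becomes aware of the event.
- In *Intervention safety* and *Statistical analysis*, state that participants' events after AID start and all control events, including participants' own events before AID start, are taken from the same national admission and mortality records with the same definitions. State that self-reports are used for safety monitoring only.

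The cost is a few sentences in the protocol, a change to the participant instructions, and a few more reports to triage.
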